#### Sample Size

We aim to recruit 300 families to the study, 150 to the intervention group (Volunteer Family Connect + usual services) and 150 families to the control group (usual services). Recruitment of 150 families per group has been undertaken based on what is feasible given current caseloads in the participating sites and also so that, allowing for attrition, data analysis can be conducted with a final sample size of 100 families per group. A sample size of 100 families per group has power of .80 at the 95% level to detect effect sizes (ESs) of .5 or larger for the PSCS Satisfaction subscale (significant differences detected with minimum n=16 per group) and the Client Enablement Index (significant differences detected with minimum n=7 per group) based on pilot study findings and a previous trial of nurse home visiting conducted by one of the chief investigators on this study [34].

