**Figure 2 figure2:**
[figure not shown]
Participant flow diagram.

The families will participate in data collection for a period of 15 months. Strategies have been put in place to support and encourage the retention of participants, including asking all participating parents to provide the name and phone number of a relative or friend who can be contacted by the researchers if we struggle to reach them; providing families with the contact details of the research team and asking them to advise us if their contact details change; providing each family with an Aus $20 gift voucher for a popular grocery store chain at each data collection point and sending thank you notes; and employing project offices who have strengths in the building of rapport with families. The decision to employ these strategies was primarily based on the positive experiences of the research team in the previous research projects [34,35].

A total of 80 volunteers and 80 comparison group members will be recruited to the study, reflecting current volunteer numbers.

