Program Coordinators: Each site has an employed program coordinator with tertiary qualifications in social work or a related field. The program coordinators are responsible for recruiting and training the volunteers, establishing referral networks, matching volunteers with families, providing regular supervision to volunteers, conducting intake and progress interviews with families, and referring families to other services within the community.Trained volunteers: All community volunteers participate in a minimum of 30 hours of training before being matched with a family and must participate in two additional capacity-building sessions each year. Examples of core training modules include “a strengths-based approach to working with families,” “reflection on personal values and attitudes,” “boundaries and self-care,” “child development,” and “community resources.” The topics for ongoing capacity-building sessions are decided by the program coordinator depending on family needs at the time. For example, if there are high numbers of families who have infants, topics like “breastfeeding” or “sleeping and settling” may be chosen. All volunteers undergo a background check.Matching: Program coordinators match families with a volunteer, guided by the needs of the family but limited by the pool of volunteers available.Home visits: Volunteers visit the family for approximately 2 hours every week. What happens during visits will depend on the needs of the family. Volunteers are encouraged to support families to connect with other services and facilities within the community (eg, attend local playgroups, visit the child and family health center, go to the park, etc) and link them with information as needed. Volunteers are also expected to model positive interactions with the children and encourage the parents in their personal and family goals. Volunteers do not do cooking or housework tasks unless it is with the parent as part of helping them to learn how to do these tasks, and they do not provide child-minding or child care such as changing nappies or bathing children. Volunteers complete checklists following each home visit, detailing the activities and topics of discussion with the family and whether information was provided to the family or the family linked with another service in the community. The collated data are used as a measure of program fidelity and provide ongoing quality feedback to the service partner organizations.Exit interviews: The duration of the service will be a minimum of 3 months and a maximum of 12 months. When the family, volunteer, and program coordinator agree that the family has met their goals, the family is exited from the program and referred to other services by the program coordinator as appropriate.

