### Data Analysis

#### Quantitative Analysis

Primary and secondary outcomes will be extracted and analyses conducted using SPSS Version 25.0. Analysis will be completed both on an intention-to-treat and a per-protocol basis. Families will be considered to have received the scheduled dose if they receive visits from the volunteer for at least 3 months with no gap between visits of more than 2 weeks. Volunteer outcomes will be analyzed using cross-sectional comparative analysis. Participant demographic data will be analyzed using basic descriptive statistics. Prior to the analysis of outcome measures, data will be assessed for outliers and normality. Scale variables will be analyzed using independent *t* test or analysis of variance or their nonparametric counterparts (eg, Mann–Whitney U test) if appropriate. Mixed modeling will be completed on the primary and secondary family outcomes to assess the effect of the intervention over time while adjusting for possible confounders. Categorical variables will be analyzed using odd ratios or chi-square analysis. For all analyses, two-tailed tests will be undertaken: findings with α<0.05 will be determined to be statistically significant. ESs will be calculated for all trends (α<0.1) and statistically significant findings; (ES≈0.5 [Cohen *d*]) will be considered clinically meaningful. Overall, the program will be considered to have been effective if at least one of the primary outcomes is positive and the other is neutral.

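### Intervention families probably share volunteers, yet the named independent-samples tests ignore this and the plan does not say whether they or the mixed model decide effectiveness; the effect is modest

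*Protocol article*

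**What the plan says.** **Numbers.** The Sample Size section of the protocol article plans "We aim to recruit 300 families to the study, 150 to the intervention group" and the same number to control, so that after attrition "data analysis can be conducted with a final sample size of 100 families per group". It adds: "A total of 80 volunteers and 80 comparison group members will be recruited to the study, reflecting current volunteer numbers". The Abstract gives 80 as a minimum.

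**Delivery.** Under Delivery in the Trial, coordinators match each family with a volunteer, "guided by the needs of the family but limited by the pool of volunteers available". Service lasts 3 to 12 months, and volunteers complete a checklist after each visit. Control families have no volunteer. Under Allocation, most families are randomized individually.

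**Analysis.** Quantitative Analysis says "Scale variables will be analyzed using independent" t test, analysis of variance or nonparametric counterparts such as Mann–Whitney. It adds mixed modeling of the primary and secondary family outcomes, to assess the effect over time and adjust for confounders; random effects are not listed. For all analyses, "two-tailed tests will be undertaken: findings with α<0.05 will be determined to be statistically significant". The program counts as effective if at least one primary outcome is positive and the other neutral. Which analysis supplies that result is not stated.

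**The concern.** Families visited by the same volunteer share that person's skill, style and local knowledge, so their outcomes may be correlated. This can happen only in the intervention arm, which makes the design partially nested. An independent-samples test treats all families as unrelated. If volunteers differ, it understates the variance of the intervention mean, its confidence interval is too narrow, and its error rate exceeds the nominal 5%. Because the text ranks neither analysis above the other, a t test alone could supply the positive primary outcome on which the effectiveness rule turns.

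**Working it through.** **1. Does sharing follow from the document's figures?** 150 / 80 = 1.875 families per volunteer at recruitment, and 100 / 80 = 1.25 among families analysed. No sharing at all would need about 150 active volunteers. Eligibility Criteria says that halving the volunteers would harm implementation, and Allocation plans for more families than available volunteers. With service of 3 to 12 months, a volunteer can serve families in sequence. Sharing is therefore a strong inference, though families per volunteer are never stated.

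**2. The plan's own power figure.** The plan says 100 per group "has power of .80 at the 95% level to detect effect sizes (ESs) of .5 or larger". With independent families, two-sided 0.05 and the normal approximation, power at d = 0.5 is Φ(0.5/√(2/100) − 1.96) = 0.942. Power of 0.80 needs about 63 per group, and 100 per group gives 0.80 at d of about 0.40. The stated 0.80 is thus conservative, which leaves slack for clustering.

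**3. Formulas.** Let nⱼ be the number of families of volunteer j, N the families per arm, and w = Σnⱼ²/N.

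- Design effect, intervention arm only: DE = 1 + (w − 1) × ICC
- True over naive standard error: R = √((DE + 1)/2)
- True two-sided error of the naive test: 2(1 − Φ(1.96/R))
- Power at d = 0.5 using the correct standard error: Φ(0.5/(R√(2/N)) − 1.96)

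**4. Assumptions.** The document gives no ICC and no caseload distribution. I take ICC from 0.05 to 0.20, 80 volunteers, and three caseload patterns:

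- *Near-even.* 150 families: 70 volunteers with two and 10 with one, w = (70×4 + 10)/150 = 1.933. 100 families: 20 with two and 60 with one, w = (20×4 + 60)/100 = 1.40.
- *Random*, each family equally likely to go to any volunteer: expected w = 1 + (N − 1)/80, that is 2.8625 (150) or 2.2375 (100).
- *Uneven*, coefficient of variation of caseload 1: w = 2 × mean load, that is 3.75 (150) or 2.50 (100).

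**5. Results (ICC 0.05 to 0.20).**

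| Caseload | Families | DE | R | Type I error |
|---|---|---|---|---|
| Near-even | 100 | 1.020–1.080 | 1.005–1.020 | 5.1–5.5% |
| Near-even | 150 | 1.047–1.187 | 1.012–1.046 | 5.3–6.1% |
| Random | 100 | 1.062–1.248 | 1.015–1.060 | 5.4–6.4% |
| Random | 150 | 1.093–1.373 | 1.023–1.089 | 5.5–7.2% |
| Uneven | 100 | 1.075–1.300 | 1.019–1.072 | 5.4–6.8% |
| Uneven | 150 | 1.138–1.550 | 1.034–1.129 | 5.8–8.3% |

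Worked example (near-even, 150 families, ICC 0.20): DE = 1 + 0.933 × 0.20 = 1.187; R = √(2.187/2) = 1.046; 1.96/1.046 = 1.874; error 6.1%.

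Power at d = 0.5 with 100 per group is 0.934 to 0.940 at near-even loads and 0.909 to 0.935 at uneven loads, against 0.942 without clustering.

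**The case against.** **The mixed model may already handle this.** It covers the primary outcomes, and a condensed article may leave its random effects to the analysis plan. This stands: a reader might infer that every stated analysis treats families as independent, but the random effects are unspecified, not excluded. What remains is that the article does name tests that assume independence and does not say that the mixed model takes precedence.

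**The pool is not fixed at 80.** That is the recruitment figure for the volunteer study, given once as a minimum, and coordinators go on recruiting volunteers. This also stands: sharing is very probable, not certain. The Allocation example, with five available volunteers and five families allocated, points toward fairly even loads.

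**The false-positive claim needs a particular null.** If volunteers have no effect on any family, they create no correlation and no inflation. Type I error rises only if volunteers differ while averaging zero. At ICC 0.20 the between-volunteer standard deviation is √0.20 = 0.45 outcome standard deviations, close to the 0.5 that the plan calls clinically meaningful, so the upper end is demanding. The same percentages, however, are also the non-coverage of the nominal 95% interval, which applies whatever the average effect.

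**Volunteers could be regarded as fixed.** Study Design describes a pragmatic test with the partners' current volunteers, and for that workforce differences between them need not count as sampling error. That is a defensible estimand, so it would be too strong to say that the result cannot be generalized. But the Introduction wants the results to inform public policy, which reaches beyond the present volunteers.

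**Conclusion.** The point holds in a limited form. The tests named in the article ignore probable one-arm clustering by volunteer, and the text leaves open whether they decide the primary result. With 80 volunteers and an assumed ICC of 0.05 to 0.20, the true standard error is about 0.5% to 5% above the naive one at near-even caseloads (type I error about 5.1% to 6.1%, from 100 analysed to 150 recruited families). At uneven caseloads it is up to about 13% above (about 8.3%). All of this is conditional on volunteers differing in effect.

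A reader might infer a seriously inflated error rate or an underpowered trial. The documents support neither: error rates in double figures would need far fewer active volunteers than the stated 80, and power at d = 0.5 stays well above 0.80. This is an inexpensive improvement, not a threat to the design.

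**What to change.** State in Quantitative Analysis that the mixed model is the deciding analysis of each primary family outcome. Give it a random intercept for volunteer in the intervention arm only, with each control family as its own cluster, and small-sample degrees of freedom such as Satterthwaite. Link each intervention family to its first matched volunteer through the visit records, and keep the independent t test or ANOVA as descriptive.

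The cost is some wording and a volunteer identifier in the analysis file; visit checklists are already collected, so the link should be recoverable. Intervals become slightly wider, by a few per cent at near-even loads. The volunteer variance may be imprecise or estimated at zero, because many volunteers will have only one family; the plan should say how such a fit will be reported.

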**Methods:**

The RCT is being conducted in 7 sites across Australia. We aim to recruit 300 families to the study: 150 control (services as usual) and 150 intervention (services as usual + volunteer home visiting) families. Intervention families will receive the service for 3-12 months according to their needs, and all participants will complete 6 data collection points over 15 months. A minimum of 80 volunteers will also be recruited, along with a matched community comparison group. The volunteers will complete 3 data collection points over 12 months. Primary outcomes include community connectedness and parenting competence. Secondary outcomes include parent physical and mental health; general parent well-being; parent empowerment; the child-parent relationship; sustainability of family routines; child immunization; child nutrition or breastfeeding; number of accidental injury reports; and volunteer health, well-being, and community connectedness.

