### Hypothesis

Families receiving a volunteer home visiting service intervention will have significantly better family outcomes at 15 months post program entry (higher sense of parenting competence and stronger community support networks) than those allocated to continue to receive usual community-based support services.

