
#### Control Group, Services as Usual

Neither intervention nor control group families are limited in the extent to which they are able to access other services within the community. It is anticipated that most families will access a range of early childhood health and education services. Family use of other services will be documented in the research, based on parent self-report, and explored as a variable in analysis.

**Table 1 table1:** Outcome measures.

Outcomes and Construct Measured			Data Collection Schedule						Instrument
			Enrollment (Baseline)	Months					
				3	6	9	12	15	

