### Data Collection, Management, and Security

Interviewers are trained in the standard administration of the instruments and handling of distressed parents or volunteers. The research team meets at least monthly to review interview techniques and ensure consistency of administration. All data are checked to ensure accuracy and consistency of data entry.

Family participants will complete a survey every 3 months for 15 months, commencing at recruitment and continuing until 15 months post their own recruitment date. The baseline and follow-up surveys will be collected by a research assistant (at the home of the participant or over the phone) or self-completed by participants if preferred. Surveys can be completed on a paper form or a word document sent via email, or they can be Web based using Qualtrics software (Qualtrics, Provo, UT). The Web-based version of the survey has been tested for usability and technical issues in one of the study sites and will eventually be rolled out to all sites. Previous research suggests that offering multiple survey response modes allows participants to choose what is most convenient for them, with little negative impact on data quality [50]. The use of iPads and Web-based survey software has been shown in the previous research to increase efficiency and reliability and to reduce data entry errors [51-53]. All data collected via paper or emailed word documents will be entered into the Web-based survey by a research assistant. Data will be stored in a password-protected Qualtrics database and backed up to a password-protected folder on a server. Only members of the research team will have access to the data.

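### The month-15 primary hypothesis has two unranked analyses, and neither is tied to month 15 or to the baseline score

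*Protocol article*

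**What the plan says.** - **Target.** The Hypothesis section expects intervention families to have "significantly better family outcomes at 15 months post program entry" on parenting competence and community support networks.
- **Data.** The abstract says "all participants will complete 6 data collection points over 15 months". Table 1 lists both primary outcomes at baseline and at months 3, 6, 9, 12 and 15.
- **First method.** After a check for outliers and normality, the Quantitative Analysis section gives scale variables an independent t "test or analysis of variance or their nonparametric counterparts (eg, Mann–Whitney U test) if appropriate". It names no visit and no covariate.
- **Second method.** The same paragraph applies mixed modeling to the primary and secondary family outcomes "to assess the effect of the intervention over time while adjusting for possible confounders". It names no visit contrast, lists no confounders and does not mention the baseline score.
- **Decision rule.** The program counts as effective if one primary outcome is positive and the other neutral, with two-sided tests at 0.05. Intention-to-treat and per-protocol analyses are both planned, and neither is called the deciding one.
- **Blinding.** The Allocation section says that data analysis will be blind and done by team members who took no part in data collection.

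**The concern.** The primary outcomes are scale scores measured on families, so both method sentences cover them as written. A reader cannot tell which p value would make an outcome positive under the decision rule.

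The two methods also need not estimate the same quantity. An effect over time may be a slope, an average over visits or a contrast at one visit, and only the last, taken at month 15, answers the stated hypothesis. The difference is real here: families leave the program at any point from month 3 to month 12, and follow-up runs to month 15 so that at least one measurement falls after exit. A trajectory that rises during the service and flattens or fades afterwards is quite possible.

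Two things are at stake. The first is error control, if the more favourable analysis could be reported as the deciding one. The second is efficiency, if the unadjusted test decides, because that test ignores the baseline score and every family missing at the visit analysed.

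**Working it through.** **1. The plan's own figure.** The Sample Size section gives power .80 with 100 families per group for effect sizes of .5 or larger. For an unadjusted two-sided test at 0.05:

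- Power = Φ(d·√(n/2) − 1.96) = Φ(0.5 × 7.071 − 1.96) = Φ(1.576) = 0.942 (0.940 by the noncentral t).
- 80% power at d = 0.5 needs 63 per group (64 by t).
- Detectable d at 80% power with n = 100: (1.960 + 0.842) × √(2/100) = 0.396.

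The stated .80 does not reproduce, but the mismatch is on the safe side.

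**2. What baseline adjustment is worth.** The baseline to month-15 correlation r is not in the protocol, so 0.4 to 0.7 is an assumption. Adjustment multiplies the variance by 1 − r².

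| r | 1 − r² | 100 adjusted per group act like | detectable d, 80% power | power at d = 0.5 | power at d = 0.3 |
|---|---|---|---|---|---|
| none (unadjusted) | 1.00 | 100 | 0.396 | 0.942 | 0.564 |
| 0.4 | 0.84 | 100/0.84 = 119 | 0.363 | 0.971 | 0.639 |
| 0.6 | 0.64 | 100/0.64 = 156 | 0.317 | 0.993 | 0.755 |
| 0.7 | 0.51 | 100/0.51 = 196 | 0.283 | 0.999 | 0.844 |

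At d = 0.5 there is little left to gain. At d = 0.3 the gain is large.

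**3. Missing families.** The plan allows for 150 per group falling to 100, which is 50/150 = 33%. A t test at a given visit uses only the families seen at that visit. A mixed model can use the earlier visits of those lost later.

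**4. A slope is not the month-15 difference.** Code the six visits 0 to 5 (mean 2.5, sum of squared deviations 17.5). Suppose the arms differ by d from month 3 onward and stay so. The month-15 difference and the post-baseline average are then both d. The fitted linear slope is (−1.5 − 0.5 + 0.5 + 1.5 + 2.5)d/17.5 = 0.143d per interval, or 5 × 0.143d = 0.71d over 15 months. Even this simple profile separates the targets. If the effect fades after exit, the average differs from month 15 as well.

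**5. False-positive rate if either analysis may count.** This was simulated under no effect for one outcome, with 100 per group, six visits, complete normal data and 6,000 replicates per setting. The correlation was 0.5 between all visits, 0.7 between all visits, or decaying with distance (0.7 raised to half the number of visits apart). A per-family linear slope and a baseline-adjusted post-baseline mean stood in for mixed-model effects. Each test alone gave about 5%.

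| Counted as positive if either is significant | Two-sided error |
|---|---|
| Month-15 t test or Mann-Whitney | 5.4% to 6.1% |
| Month-15 t test or baseline-adjusted average | 8.2% to 8.8% |
| Month-15 t test or linear slope | 9.2% to 9.3% |

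The simulation error of the last row is about √(0.09 × 0.91/6000) = 0.4 percentage points. The rule of one positive outcome out of two adds a separate multiplicity, which is not counted here.

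**The case against.** The strongest reply is that this is a condensed article and the full analysis plan is not shown. Time coding, the named contrast and the covariate list commonly belong in that plan. The only method sentence that names the primary family outcomes is the mixed-model one. The t test sentence is worded by variable type, parallel to the one on categorical variables, and may be meant for volunteer or descriptive comparisons. On that reading there is one primary analysis, and a mixed model that includes the baseline wave already captures the gain in step 2.

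Part of this stands. The absence of a covariate list or a covariance structure is no fault in an article. But the scale-variable sentence carries no limit to volunteers and directly follows one about outcome measures. No ranking is given, and the model's stated target is not that of the hypothesis. Those are statements in the text, not detail left out of it.

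Some stronger readings are tempting, and the protocol does not support them:

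- **The plan is a completer analysis, not intention-to-treat.** It states intention-to-treat and includes a mixed model. The loss of families applies only if the t test decides, and the t test is not fixed to month 15.
- **The primary model adjusts for service use, a consequence of the program.** The control-group section says only: "Family use of other services will be documented in the research, based on parent self-report, and explored as a variable in analysis". It is never named as a covariate of the primary model, and Table 1 lists service use among the secondary outcomes.
- **The 15-month clock is contradictory, because controls have no program entry.** The data collection section settles it for all families: surveys run from recruitment, "continuing until 15 months post their own recruitment date". The Hypothesis wording is loose, no more.

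**Conclusion.** The point holds in limited form. The protocol fixes the primary hypothesis at 15 months but gives the primary scale outcomes two unranked analyses. Neither is tied to that visit or to the baseline score, and the success rule does not say which one decides. This should be settled before results are seen.

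The size is moderate. A reader might infer that the trial is underpowered. It is not: with 100 per group the unadjusted test has about 94% power at the plan's own effect size of 0.5. What is lost on the unadjusted route is precision and power for smaller effects, by an amount that rests on an assumed correlation of 0.4 to 0.7.

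A reader might also take about 9% as this trial's false-positive rate. It is the rate for one outcome and one pair of analyses, with the better result always taken. Other pairs give less, and blind analysis limits favourable selection without removing it. What the text supports is that the rate exceeds 5% if either analysis may count.

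**What to change.** Name one deciding analysis for each primary outcome:

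- an intention-to-treat mixed model for repeated measures using all post-baseline visits, with baseline score, arm, visit as a category and arm-by-visit;
- any further covariates listed in advance and limited to variables measured before randomization;
- the primary estimate defined as the arm contrast at 15 months from recruitment (randomization), and this result alone deciding whether the outcome is positive.

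Label the t test, ANOVA, rank tests and per-protocol analysis as supportive.

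The cost is a few sentences. Baseline and all five follow-up scores are already collected, and mixed modeling in the named software is already planned. No change to sample size or data collection is needed.

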**Primary Outcomes**									
	Community connectedness		✓	✓	✓	✓	✓	✓	Community Connectedness Scale [37]; Social Provisions Scale [38].
	Parenting competence		✓	✓	✓	✓	✓	✓	Parenting Sense of Competence Scale [39].

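### Success on either of two primary outcomes, each tested at an unadjusted two-sided 0.05, raises the chance of a false effectiveness verdict to about 4.2–4.8% against 2.5% for a single test

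*Protocol article*

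**What the plan says.** All of the following is in the protocol article.

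- **Success rule** (Quantitative Analysis): "the program will be considered to have been effective if at least one of the primary outcomes is positive and the other is neutral".
- **Significance level** (same section): "two-tailed tests will be undertaken: findings with α<0.05 will be determined to be statistically significant". The sentence covers all analyses. No split of alpha, testing order or other adjustment is given.
- **Primary outcomes** (Abstract, Methods): "Primary outcomes include community connectedness and parenting competence".
- **Instruments** (Table 1): parenting competence has one, the Parenting Sense of Competence Scale. The entry for community connectedness is "Community Connectedness Scale [37]; Social Provisions Scale [38", with no lead scale and no combined score.
- **Time point** (Hypothesis): 15 months after program entry.
- **Analysis sets** (Quantitative Analysis): "Analysis will be completed both on an intention-to-treat and a per-protocol basis". Neither set is named as the one that decides.
- **Power** (Sample Size): .80 with 100 analysed families per group for effect sizes of .5 or larger, stated for the satisfaction subscale of the parenting competence scale and for an enablement index. No power figure is given for connectedness.

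**The concern.** When success can be reached through either of two outcomes and each is tested at the full 0.05, the error rate of the conclusion is larger than that of each test. Here the article itself fixes both halves of the problem, the either/or rule and the single alpha for all analyses. It is therefore not a detail left to an analysis plan: a later plan that split alpha would depart from the published text.

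The second weakness lies in the connectedness outcome. If one of its two scales is significant and the other is not, the article does not say whether the outcome counts as positive or neutral. The success rule cannot then be applied without a choice made after the results are known.

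This rule produces the overall answer of a trial whose results, according to the Introduction, can be used to inform public policy.

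**Working it through.** **Inputs.** Per-test alpha is two-sided 0.05, so 0.025 in the favourable direction (Quantitative Analysis). There are two primary outcomes (Abstract) measured by three scales (Table 1). The analysed sample is 100 per group and the effect size 0.5 (Sample Size). The correlation between the test statistics is not given; I assume a range of 0 to 0.7 and show 0.9 as an extreme. Positive is read as significant at 0.05 in favour of the program, neutral as not significant, and two positive outcomes are taken to count as effective.

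**Step 1, the plan's own power figure.** A two-sample t test with 100 per group, d = 0.5 and two-sided 0.05 has power 0.940. Power of 0.80 needs 64 per group. The stated .80 is therefore correct only as a minimum, and there is room to spend.

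**Step 2, two tests under the actual rule, no true effect.** A verdict of effective requires that no outcome be significantly negative and that not all be neutral:

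P(effective) = P(none negative) − P(all neutral)

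If independent: 0.975² − 0.95² = 0.9506 − 0.9025 = 0.0481, which is 1.9 times 0.025.

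Ignoring the condition that the other outcome be neutral would give 1 − 0.975² = 0.0494, so that condition removes very little.

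**Step 3, three tests.** This applies only if either connectedness scale alone can make that outcome positive and no scale may be significantly negative. If independent: 0.975³ − 0.95³ = 0.9269 − 0.8574 = 0.0695, which is 2.8 times 0.025.

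**Step 4, correlated tests.** The same probability, with equally correlated normal test statistics:

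| Assumed correlation | Two tests | Ratio to 0.025 | Three tests | Ratio to 0.025 |
|---|---|---|---|---|
| 0 | 0.048 | 1.9 | 0.069 | 2.8 |
| 0.3 | 0.047 | 1.9 | 0.068 | 2.7 |
| 0.5 | 0.045 | 1.8 | 0.063 | 2.5 |
| 0.7 | 0.042 | 1.7 | 0.055 | 2.2 |
| 0.9 | 0.035 | 1.4 | 0.042 | 1.7 |

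**Step 5, after adjustment.** Two primaries at 0.025 each, independent: 0.9875² − 0.975² = 0.9752 − 0.9506 = 0.0245, back to the single-test level. Power at d = 0.5 with 100 per group is 0.898. The effect detectable with 80% power moves from d = 0.40 to d = 0.44, and about 78 per group suffice for 80% power at d = 0.5.

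**The case against.** Several objections limit the point, and most of them stand in part.

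- **The larger two-sided figures.** A reader might quote 1 − 0.95² = 9.8% or 1 − 0.95³ = 14.3%. These count harmful findings as well. The rule requires a favourable result and no significant loss on the other outcome, so they do not describe it. The like-for-like comparison is with 2.5%. Against the only alpha the article states, 0.05, the two-test rate of 4.8% would not look inflated. The answer is that a single primary tested two-sided at 0.05 would give a false favourable verdict 2.5% of the time.
- **The three-test figure.** The rule counts outcomes, not scales, and the article does not say that either connectedness scale suffices. This stands: 5.5% to 7% is conditional, and it would be conjecture to say that the better scale will be chosen.
- **The meaning of positive.** The same section calls an effect size near 0.5 clinically meaningful. With 100 per group, significance at 0.05 needs an observed d of about 0.28, whereas an observed d of 0.5 corresponds to p of about 0.0005. If positive also required an effect of that size, the inflation would all but vanish. The article does not make that link; the only threshold it gives for calling a finding significant is 0.05.
- **The hypothesis.** It expects "higher sense of parenting competence and stronger community support networks", and a reader might infer a contradiction between a joint hypothesis and an either/or rule. The documents do not support that. The hypothesis lists the expected benefits in a parenthesis, while the analysis section gives the operational rule. One can expect both and accept one.
- **Analysis set.** Which set leads is commonly settled in the analysis plan, so its absence here is not an error in itself. It matters only because the meaning of a positive outcome depends on it.

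**Conclusion.** The concern holds in a limited form. The article fixes an unadjusted either/or rule for its headline verdict, and the chance of a false declaration of effectiveness is about 4.2% to 4.8%, against 2.5% for a single test (1.7 to 1.9 times). This rests on reading positive as significant at 0.05 in the favourable direction and on assumed correlations from 0.7 down to 0. If either connectedness scale alone could make that outcome positive, the rate is about 5.5% to 7% (2.2 to 2.8 times). A flat statement that the error rate is two to three times nominal would go too far: it sits close to the independence ceiling, and its upper part needs that unstated premise.

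The unclear scoring of connectedness is a defect whatever the error rate, because a split result between the two scales leaves the rule without an answer.

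**What to change.** Keep the either/or rule and complete it:

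1. Name one connectedness scale, with its score, as primary and make the other secondary.
2. Test the two primaries with Holm, or Bonferroni at 0.025 each, at a family-wise two-sided 0.05, and exempt them explicitly from the sentence that sets 0.05 for all analyses.
3. Define positive as significance on the adjusted test in the favourable direction, and state that the intention-to-treat contrast at month 15 decides it, with the per-protocol analysis as supportive.

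Rewording the hypothesis to match the rule is optional. Requiring both outcomes to be positive would also remove the need for adjustment, but it would redefine success while data collection is under way, and I do not recommend it.

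**Cost.** The change is to the analysis text and needs no extra families. It should be made before anyone sees outcomes by group. With 100 analysed per group, power for an effect size of 0.5 falls from 0.94 to 0.90 per outcome under Bonferroni, still above the planned .80; Holm loses no more than that. For connectedness the figure applies only if an effect size of 0.5 is assumed, since the article gives no power calculation for that outcome.
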